## Cardio-pulmonary and renal MRI

Cardiovascular MRI is the reference diagnostic method for myocardial injury, including myocarditis and acute cardiomyopathy. Stress perfusion MRI using intravenous adenosine enables dynamic imaging of myocardial blood flow during stress and rest conditions. In-line pixel mapping enables fully quantitative read-out of myocardial blood flow (mL/min/g tissue), classified at a subsegmental level (32 myocardial segments) with the percentage extent of myocardium with impaired perfusion during stress (% ischaemic burden).^61–66^ All of this information can be spatially mapped with LV function, tissue characteristics revealed by T2-mapping, native T-mapping, LGE, and extracellular volume (ECV).^52^ In this study, the modified Lake Louise criteria will be used to diagnose definite myocardial inflammation [T2 map + T1 (native T1, LGE, or ECV abnormal)] or probable myocardial inflammation (either T2 or T1 abnormal).^49^^,^^50^ In order to limit selection bias, renal dysfunction is not an exclusion criterion. Patients with severe renal dysfunction [glomerular filtration rate (GFR) <30 mL/kg/m^2^] will be considered for contrast MRI according to local radiology protocols.

SARS-CoV-2 causes vascular dysfunction and microthrombotic angiopathy.^10^ Our scientific hypothesis is that microvascular dysfunction underlies the cardiovascular toxicity caused by this infection through primary and secondary mechanisms. Direct virus infection of injured endothelial cells, disrupting the integrity of the endothelial barrier, permits virus infection of deep tissues, causing myocarditis and nephritis. Myocarditis and ischaemia may induce cardiomyopathy leading to left and right ventricular dysfunction. Secondary consequences of COVID-19 including hypoxia, inflammation, and vasospasm impaired tissue perfusion, leading to myocardial ischaemia.

MRI will be undertaken at 3.0 Tesla (Siemens PRISMA) ∼28 days after discharge. This timepoint may be considered as the subacute, convalescent phase. The rationale for undertaking the multiparametric, stress perfusion cardiovascular MRI at this timepoint is to determine whether there is persisting evidence of myocardial injury and/or MI, LV function, and incidental pathology (e.g. mural thrombus) in the convalescent phase. The patients will be advised to withhold cardiovascular medications and to avoid caffeine-containing drinks for 24 h before the scan.

MRI will also provide information for incidental findings in the chest (e.g. pulmonary arterial thrombus) and abdomen. Imaging of renal anatomy, size, and tissue characterization will be exploratory.

## Computed tomography

The CT scanner has 320 detectors enabling full heart coverage within a single heartbeat (Aquilion ONE, Canon). Intravenous metoprolol will be used where required to control the heart rate (target 60 b.p.m.) and sublingual glyceryl trinitrate will be given to all patients immediately before the scan acquisition. An initial low radiation dose helical scan of the thorax will be acquired for comprehensive assessment of the lungs. A contrast bolus timing scan will be acquired which will provide information on cardiopulmonary transit times. Non-contrast and contrast-enhanced angiographic breath-hold ECG-gated volumes will be acquired timed for optimum pulmonary and systemic arterial (coronary) opacification.

CTCA will provide information on the presence and extent of coronary calcification (calcium score), CAD, and whether CAD is obstructive (flow-limiting) including the CAD-RADS score. Intracardiac thrombus will be assessed. Late enhancement ECG-gated CT will be acquired to assess for delayed enhancement (scar)^67^ and ECV calculation.^68^ Pulmonary vascular imaging will assess pulmonary vascular thrombosis (embolism) including CT obstruction score, cardiopulmonary transit times, and measures of raised pulmonary artery (PA) and right heart pressures [PA, caval and azygous dimensions plus hepatic inferior vena cava (IVC) reflux]. CT will also characterize pulmonary features associated with COVID infection (percentage ground-glass opacity, percentage consolidation, and CO-RADS score) plus pre-existing lung damage (percentage chronic obstructive pulmonary disease). CT will also assess for signs of osteoporosis and sarcopenia as frailty markers.

The CT and MRI findings will be correlated with the other clinical data. Cardiac and extracardiac findings will be reported and managed according to local standards of care. Patients with severe renal dysfunction thought to be at risk of acute kidney injury as determined by local radiology clinical protocols will undergo non-contrast CT.

## Natural history

In order to assess the natural history, longer term follow-up for health outcomes will be undertaken using electronic record linkage, removing the need for participants to undergo further research visits after the 12-month visit.

## Exploratory analyses

The scans will be pseudoanonymized, i.e. identifiers removed and assigned a unique study number to enable linkage. The scans will be shared with research collaborators for cardiovascular modelling to better understand the relationships between tissue pathology, blood flow, and function.

COVID-19 infection and treatment are associated with changes on the ECG. The changes include alterations in heart rate, conduction, and ventricular repolarization. Drug treatment for COVID-19 may prolong the QTc interval. Whether these changes persist after the acute phase and their relationships to myocardial pathology are unknown. Paper and/or digital ECGs will be acquired, de-identified, and provided to the University of Glasgow Electrocardiography Core Laboratory for automated analysis. The ECG measures will be linked with the clinical and imaging data.

We will undertake exploratory research into the vascular biology of COVID-19 infection. This work will be undertaken in collaboration with cardiovascular scientists and virologists in the University of Glasgow. We will study the vascular biology of cells and molecules (e.g. RNA and cytokines) implicated in SARS-CoV-2. Informed consent will be obtained for post-mortem examination in the event of death during the study period. Histology samples of the heart will be examined for features of myocarditis, MI, and microvascular disease. The histopathological findings will be linked to the CMR findings.

## Feasibility

This study has been developed with input from members of a multidisciplinary research team and the Scientific Strategy Group of the University of Glasgow. The study has been peer reviewed by panel members of the Chief Scientist Office of the Scottish Government. The study has been reviewed by the Patient and Public Involvement group of NHS Greater Glasgow and Clyde Health Board.

## Statistical considerations

The statistical analyses will be pre-defined according to a Statistical Analysis Plan.

### Sample size calculation

The primary outcome is myocarditis (myocardial inflammation). To detect an association between a history of pre-existing cardiovascular disease and the incidence of myocardial inflammation (myocarditis) at 2–4 weeks, we have assumed 25% of patients with prior cardiovascular disease and the incidence of myocardial inflammation in those with/without prior cardiac problems to be 33% and 10%, respectively. To have 80% power to detect this difference will require 140 participants (35 with cardiac problems, 105 without) to be scanned. We aim for 160 patients to attend the imaging visit, anticipating that 10–15% of the participants may have incomplete imaging data due to technical reasons such as imaging artefact or claustrophobia.

Pre-specified subgroup analyses are intended for patients without cardiovascular disease, as defined by the absence of (i) prior cardiovascular disease and (ii) obstructive CAD on CTCA. Given the public health significance of COVID-19, interim reports may be undertaken.

### Blinding

Outcome assessments (endpoint adjudication) will be undertaken in blinded fashion. The primary outcome evaluation (myocardial injury endotype) will be adjudicated by a panel of cardiologists blind to the clinical status of the patient and performed according to a pre-specified charter.

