## Study procedures

The current protocol involves two visits. The first visit involves informed consent and baseline assessments. The second visit occurs at 28 days after discharge. A third visit is intended at 1 year, contingent on additional funding and a protocol amendment being secured. A proposed vascular biology substudy involves a gluteal skin biopsy after 28 days. The participants will be invited to consent for life-long follow-up using electronic record linkage without direct contact.

The study assessments involve gathering information from standard of care procedures and research tests. The standard of care information includes demographics, medical history (including multimorbidity), limited examination, laboratory and radiological tests, cardiology tests (including an ECG and an echocardiogram if clinically indicated), and treatment. The research assessments at both visits include blood and urine samples, a 12-lead digital ECG (Beneheart R3, Mindray), health status questionnaires, and assessments of adverse events. Visit 2 involves cardiovascular imaging, including stress perfusion MRI and CTCA, and an ECG. By designating imaging during the convalescent phase, at 28 days post-discharge, the participants are not anticipated to be infectious. This approach aligns with other contemporary studies, such as the International Severe Acute Respiratory and Emerging Infection Coronavirus Clinical Characterisation Consortium-4 (ISARIC-4C) study.^55^ Since MRI and CTCA are appropriately not performed during the acute phase, some pathologies that might have been detected acutely may have resolved by 28 days. Therefore, all clinical information obtained during Visits 1 and 2 will be used to inform the diagnosis of myocardial injury.

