#### Consensus-based diagnosis of the primary outcome

A panel of three or more cardiologists will assess the clinical information to make a diagnosis (endotype) and related certainty (Not/unlikely = no; Probable/very = yes) before and after disclosure of the MRI and CTCA findings. The diagnosis will be based on consensus. This approach reflects the uncertainty in determining a diagnosis in patients with myocardial injury. The diagnosis draws upon clinical information and test results, rather than any single test modality in isolation.

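### The primary-outcome panel is described as blind to clinical status and as diagnosing from clinical information, and nothing says prior cardiovascular disease, the exposure that sets the sample size, is withheld from it

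*Protocol article*

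**What the plan says.** Three sections of the protocol article describe how the primary outcome is judged.

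- **Blinding** (under Statistical considerations): the primary outcome evaluation, which this section equates with the myocardial injury endotype, is "adjudicated by a panel of cardiologists blind to the clinical status of the patient". It is to follow a charter written in advance, which is not shown.
- **Consensus-based diagnosis of the primary outcome**: this section sets the task as follows: "A panel of three or more cardiologists will assess the clinical information to make a diagnosis (endotype) and related certainty", once without and once with the MRI and CTCA findings. The section adds: "The diagnosis draws upon clinical information and test results, rather than any single test modality in isolation".
- **Study procedures**: because some pathology may have resolved by the time of imaging, "all clinical information obtained during Visits 1 and 2 will be used to inform the diagnosis of myocardial injury". The same section lists medical history, including multimorbidity, among the standard-of-care information collected.

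The **Sample size calculation** rests on one comparison: "To detect an association between a history of pre-existing cardiovascular disease and the incidence of myocardial inflammation (myocarditis) at 2–4 weeks".

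**The concern.** A panel that diagnoses from the clinical information, starting before any imaging is shown, is not blind to clinical status in the ordinary sense of those words. The article does not define the term more narrowly.

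The conflict matters because of what the clinical information contains. Prior CVD is part of the medical history, and it is the exposure in the comparison on which the study is sized. The outcome is a consensus judgement in which graded certainty is reduced to yes or no, with probable counted as yes. If the judges know the exposure, their threshold may differ between exposed and unexposed patients. The resulting misclassification could create an association or hide one. Once the panel has seen the history, the effect cannot be undone. The design as written also lacks the protection that the blinding statement claims for it.

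**Working it through.** **1. The passages side by side.** The Blinding section and the consensus section both describe a panel of cardiologists judging the primary outcome, so they concern the same adjudication. Study procedures names no panel, but it speaks of the diagnosis of myocardial injury, and the Blinding section labels the primary outcome the myocardial injury endotype. That the panel sees prior-CVD history is therefore a reasonable inference, not an explicit statement. No section says the history is removed.

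**2. The plan's own figure.** Inputs from Sample size calculation: "we have assumed 25% of patients with prior cardiovascular disease", so the ratio r is 3 unexposed to 1 exposed; incidence "in those with/without prior cardiac problems to be 33% and 10%, respectively"; power 80%. Alpha is not stated; two-sided 5% is assumed.

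- Pooled rate: (0.33 + 3 × 0.10)/4 = 0.1575.
- Without continuity correction: n₁ = [1.960 √((1 + 1/3) × 0.1575 × 0.8425) + 0.842 √(0.33 × 0.67 + 0.10 × 0.90/3)]² / 0.23² = 29.4, which rounds up to 30 (120 in total).
- With continuity correction: n₁ = (29.35/4) × [1 + √(1 + 2(1 + 1/3)/(29.35 × 0.23))]² = 34.9, which rounds up to 35.
- Total: 35 + 105 = 140, as stated.

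The sample size is not in dispute, and no corrected number follows from this point.

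**3. What differential classification could do.** The shifts below are assumptions; the article gives no misclassification rates. The method is exact enumeration of two binomials, n = 35 and 105, adding the probability of every table for which Fisher's two-sided p is below 0.05.

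*Upward shift, no true difference (10% in both groups):*

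| Observed rate, prior CVD | Observed rate, no prior CVD | Chance of a significant result |
|---|---|---|
| 10% (no shift) | 10% | 3.4% |
| 15% (+5 points) | 10% | 11% |
| 20% (+10 points) | 10% | 30% |
| 25% (+15 points) | 10% | 53% |

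*Downward shift, true rates as planned (33% versus 10%):*

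| Observed rate, prior CVD | Observed rate, no prior CVD | Power |
|---|---|---|
| 33% (no shift) | 10% | 84% |
| 28% (−5 points) | 10% | 66% |
| 23% (−10 points) | 10% | 44% |

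**4. Sensitivity to test and base rate.** Here the uncorrected chi-square test is used, and the extra false positives are a fraction f of the truly negative exposed patients, so the observed exposed rate is p + (1 − p)f.

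- True rate 10% in both groups: f = 0, 5, 10 and 15% gives 4.7%, 13%, 31% and 53%.
- True rate 15.75% in both groups (the overall rate implied by the plan): the same values of f give 4.8%, 10%, 22% and 38%.

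The pattern is the same, and the effect is smaller at the higher base rate.

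**The case against.** **The charter may settle it.** The charter is not shown, and neither is the figure on primary outcome evaluation. Either might define clinical status narrowly or list what the panel receives. This stands in part. A reader might infer that any later claim of blinded adjudication would be untrue; the article does not support that, because the unseen charter may restrict the term. But this is not a complaint about missing detail. The article makes two positive statements that conflict as worded, and its text should be made consistent.

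**The diagnosis is anchored in imaging criteria.** The modified Lake Louise criteria define definite and probable myocardial inflammation. This limits the room for judgement but does not remove it. The consensus section says the diagnosis does not rest on one modality, and its stated reason for using a panel is diagnostic uncertainty.

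**The direction of bias is unknown.** This stands. A reader might infer that knowledge of prior CVD would inflate the association. A panel that knows of an old infarct could equally assign scar to the infarction endotype and lower the inflammation rate in exposed patients. Hence both directions are shown.

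**The pre- or post-disclosure call.** A reader might infer that it is open which of the two diagnoses is primary. The natural reading is the post-disclosure one, since a call made before MRI cannot meet CMR-based criteria.

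**Full information is deliberate.** Endotypes need the clinical picture. A reader might infer that a history-redacted call should become the primary outcome. The article does not support that. CTCA and late enhancement partly reveal the exposure anyway. Late enhancement is also a T1 criterion, one abnormal criterion makes inflammation probable, and probable counts as yes. Old scar read without history could therefore add false positives among the exposed.

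**The comparison is one objective among several.** True: the primary outcome itself is a proportion. But this comparison sets the sample size, and the question it answers is a listed objective.

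**Conclusion.** The conflict is real as worded: blindness to clinical status cannot be squared with a diagnosis drawn from the clinical information unless clinical status is given a narrower meaning that the article does not supply. The article does not say that prior CVD is withheld from the panel, so differential classification by exposure is possible in the comparison that sizes the study. It is not shown to occur, and neither its size nor its direction can be derived from the document.

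The figures in the working are illustrations. They rest on assumed shifts confined to the prior-CVD group, a 35 to 105 split, and a two-sided 5% test. They show that modest shifts in either direction would be enough to matter at this sample size.

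**What to change.** **Reconcile the text.** Study procedures, the consensus-based diagnosis section and the Blinding section should together state what the panel sees at each step and from what it is blind. If medical history is shown, drop the claim of blindness to clinical status or narrow it to what is actually withheld.

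**Keep the primary diagnosis.** The full-information consensus after MRI and CTCA disclosure remains primary, and the text should say so.

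**Add one supporting analysis.** Pre-specify that the prior-CVD comparison is also run on the imaging-only modified Lake Louise classification already described under Cardio-pulmonary and renal MRI. It should be read from the existing scans without access to prior-CVD history and locked before history is revealed.

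**Cost.** Wording in the protocol and charter, plus a little extra analysis work; no further patients or scans. Masking will be only partial: CTCA and scar can reveal coronary disease, although prior CVD as the article defines it also covers diabetes, hypertension, stroke and transient ischaemic attack, which those images do not show directly. Because old scar may also count as a T1 criterion, the imaging-only result should support the primary analysis and not replace it. The change must be made before adjudication begins.

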## Trial management and timelines

The trial will be conducted in line with the current *Guidelines for Good Clinical Practice in Clinical Trials* and STROBE guidelines.^69^ The Study Management Group (SMG) includes those individuals responsible for the day-to-day management of the study including the chief investigator, project manager, and representatives from the sponsor. The role of this group will be to facilitate the progress of the study, ensure that the protocol is adhered to, and take appropriate action to safeguard participants and the quality of the study itself. Decisions about continuation or termination of the study or substantial amendments to the protocol will be the responsibility of the sponsor. A scientific steering group will oversee the study. This study is designed to be undertaken and reported rapidly in response to the global need for information about COVID-19.

## Ethics

The CISCO-19 study is approved by the UK National Research Ethics Service (Reference 20/NS/0066).

## Registration

The ClinicalTrials.gov identifier is NCT04403607.

## Discussion

Our observational, multimodality, imaging cohort study will prospectively gather information on the cardiovascular complications and their clinical significance in COVID-19. A relatively unselected approach to patient enrolment will minimize selection bias beyond those who do not survive or who are unable to comply with the protocol. The findings will be generalizable to patients in the convalescent phase of the illness and informative for the natural history. On the other hand, the findings will not necessarily be generalizable to all patients with COVID-19, since our enrolment strategy focuses on survivors following the acute phase of the illness.

Cardiovascular MRI will be used to clarify clinical endotypes according to contemporary guidelines.^49^^,^^50^ Quantitative measurements of myocardial blood flow at stress and rest will enable focused research into coronary microvascular dysfunction that may be secondary to endotheliitis caused by SARS-CoV-2. CT imaging will clarify the presence and relevance of CAD and MINOCA, lung pathology, and pulmonary arterial thrombosis. Renal MRI will be undertaken on an exploratory basis to assess kidney size (differential volume) plus both global values and cortico:medullary ratios for T1, T2, and the apparent diffusion coefficient (ADC) for correlation with renal function. Renal dysfunction is not an exclusion criterion, reflecting the open approach to enrolment. Taken together with a comprehensive clinical assessment, laboratory tests (including renal function and urine albumin:creatine ratio), and circulating biomarkers, our study will characterize multisystem involvement of SARS-CoV-2 infection.

High-sensitivity troponin is a cardiac protein that is ubiquitously released from injured cardiomyocytes. However, troponin is not cause specific, and circulating concentrations may increase due to hypoxia, hypotension, and renal failure, as well from direct cardiac toxicity. It is unclear whether cardiovascular involvement in COVID-19 is mainly secondary to severe pneumonia, or whether there is direct viral infection of the heart and blood vessels. A recent expert consensus guideline highlighted the pivotal value of CMR in the diagnosis of myocardial inflammation due to viruses, autoimmune disease, ischaemic injury, and toxic agents. MRI is diagnostically useful to identify endotypes for stratified therapy. We will assess whether this could be the case in COVID-19.

To our knowledge, CISCO-19 is the first to apply stress perfusion CMR to assess and quantify abnormalities in myocardial perfusion that may be secondary to microvascular dysfunction. The information on myocardial perfusion will help classify patients with myocardial injury into ischaemic or non-ischaemic groups. Stress perfusion MRI is not usually undertaken in patients with myocarditis, and quantitative measurements of myocardial blood flow are a key attribute of our study design. We aim to advance new knowledge into the pathogenesis of myocardial inflammation (ischaemic vs. non-ischaemic) and into the associations between the aetiology of disease and abnormalities in myocardial perfusion. Recent advances in fully quantitative, in-line pixel mapping of myocardial perfusion are uniquely enabling the quantification of myocardial blood flow in near real-time without the need for time-intensive, off-line post-processing. In addition, multimodality imaging involves multiparametric cardiovascular MRI and CTCA during the same visit. As such, our study will provide methodologically robust estimates of persisting myocardial injury and the impact on the physical and mental well-being of the participants. The results should be helpful to inform clinical management strategies for the diagnosis and management of patients recovering from COVID-19. Our study will provide complementary information to add to the growing body of knowledge on multisystem involvement in COVID-19.

We will collect information on participants’ characteristics at baseline including demographics, anthropometry, cardiovascular and medical history, and health status. The participants will be invited to give informed consent for life-long follow-up by linkage of EPRs. Using multivariable analyses, we will link the patients’ characteristics at baseline to observations during longer term follow-up in order to characterize the natural history of this condition.

Our imaging research will clarify the prevalence and clinical significance of cardiopulmonary injury (notably myocardial inflammation) in patients with COVID-19, which is a major knowledge gap in the NHS. By adopting an all-comers approach, we will identify patients with myocardial inflammation that is subclinical (i.e. not diagnosed) or clinically overt. By correlating the MRI findings with troponin and other measures of cardiovascular injury, such as BNP, our results will potentially inform NHS care pathways to use these blood tests in a more directed manner for the clinical management of patients with COVID-19. Currently, there are no disease-modifying therapies for myocarditis, including due to SARS-CoV-2.

Overall, our study will add new knowledge on the natural history of COVID-19 in a comparatively unselected population. Our study will create a unique biorepository of clinical samples and images, which in turn may be exploited by scientists undertaking mechanistic research into the vascular biology of SARS-CoV-2 infection, and cardiovascular modelling.
